## Abstract

**Background:**

Neoadjuvant endocrine therapy with an aromatase inhibitor has shown efficacy comparable to that of neoadjuvant chemotherapy in patients with postmenopausal breast cancer. Preclinical and clinical studies have shown that the antidiabetic drug metformin has anti-tumor activity. This prospective, multicenter, phase II randomized, placebo controlled trial was designed to evaluate the direct anti-tumor effect of metformin in non-diabetic postmenopausal women with estrogen-receptor (ER) positive breast cancer.

**Methods/Design:**

Patients meeting the inclusion criteria and providing written informed consent will be randomized to 24 weeks of neoadjuvant treatment with letrozole (2.5 mg/day) and either metformin (2000 mg/day) or placebo. Target accrual number is 104 patients per arm. The primary endpoint will be clinical response rate, as measured by calipers. Secondary endpoints include pathologic complete response rate, breast conserving rate, change in Ki67 expression, breast density change, and toxicity profile. Molecular assays will be performed using samples obtained before treatment, at week 4, and postoperatively.

**Discussion:**

This study will provide direct evidence of the anti-tumor effect of metformin in non-diabetic, postmenopausal patients with ER-positive breast cancer.

**Trial registration:**

ClinicalTrials.gov Identifier NCT01589367

## Background

Metformin, which is commonly used to treat type 2 diabetes, is a relatively safe drug with known pharmacokinetics and manageable toxicities. In addition, numerous experimental, epidemiologic, observational, and clinical studies have shown that metformin has anti-tumor effects [1]. For example, in a preclinical mouse xenograft model, metformin reduced the effective dosages of standard chemotherapeutic drugs and had preferential effects on tumorigenic cells [2]. A retrospective clinical study showed that patients taking metformin during neoadjuvant chemotherapy had a higher pathologic complete response (pCR) rate than diabetic patients not taking metformin or non-diabetes patients (24% vs 8% vs 16%, p = 0.02) [3,4]. Two potential mechanisms of anti-cancer action of metformin have been suggested. First, metformin may directly activate adenosine monophosphate kinase (AMPK), resulting in the downstream inhibition of mTOR signaling and the consequent suppression of cell proliferation [5-7]. Second, metformin-induced decreases in circulating insulin and insulin-like growth factor (IGF) concentrations may reduce the activation of the IGF-receptor signaling axis, resulting in decreases in growth promotion and mitogenesis [8-10]. Thus, the anti-cancer effects of metformin are mediated through a systemic improvement in metabolic profile and by directly targeting tumor cells [11,12].

Questions remain, however, about the clinical benefits of metformin as an anti-cancer agent in patients with breast cancer. Although one large-scale, phase III trial of adjuvant metformin has been initiated in women with breast cancer (NCIC CTG MA.32) [1], the accrual and treatment process is still ongoing, and several years of follow-up are needed to determine survival benefits. In addition, little is known about the effects of metformin on different subtypes of breast cancer or on the synergy between metformin and concurrently administered systemic agents. In addition, the optimal dosage of metformin that shows maximal anti-tumor effects with acceptable toxicities has not been determined. In this context, neoadjuvant treatment is the most efficient setting to assess the short-term in vivo effects of drug therapy in breast cancer patients. Neoadjuvant endocrine therapy results in a comparable response but lower toxicity compared with neoadjuvant chemotherapy in women with ER-positive breast cancer [13]. In postmenopausal women, aromatase inhibitors are associated with higher response rates than tamoxifen [14,15]. A recent phase II trial found that neoadjuvant treatment with everolimus, an mTOR inhibitor, plus letrozole resulted in a better response rate than letrozole alone [16]. In addition, neoadjuvant metformin was shown to lower Ki67 level [17]. These results suggested that metformin may be effective, when combined with letrozole, in postmenopausal women with ER-positive breast cancer. We therefore designed and initiated a phase II clinical trial evaluating the anti-tumor effect of neoadjuvant metformin in postmenopausal women with ER-positive breast cancer by comparing treatment with letrozole plus metformin or placebo.

## Methods/Design

### Study goal

The goal of this study was to evaluate the benefits of combining metformin and letrozole in the neoadjuvant treatment of postmenopausal women with ER-positive breast cancer. The primary end point is the rate of tumor response (clinical response rate) at 24 weeks, determined by measurements with calipers; changes in size on ultrasound, mammography, and MRI will be used as secondary efficacy assessments. Clinical response includes complete response (CR) and partial response (PR) by RECIST v1.1 criteria.

### Study design

METEOR is a phase II, prospective, randomized, double-blinded, placebo-controlled multicenter clinical trial. Twenty-one centers belonging to the Korean Breast Cancer Society Study Group are participating in this study (KBCSG-013). Patients will be randomly assigned (1:1) to receive letrozole 2.5 mg/day plus either metformin or placebo for 24 weeks before surgery. The initial dose of metformin will be 1000 mg/day for the first week, followed by 1500 mg/day for the second week, and 2000 mg/day from the third week onward. Patients will be randomized sequentially, stratified by center, with randomization codes. Block randomization will be used (SAS 9.2) in cooperation with the Medical Research Collaborating Center (MRCC) of Seoul National University Hospital. All study personnel will be masked to treatment. This study protocol has been approved by the Korea Food and Drug Administration (KFDA) as well as the institutional review board of each center, and was registered at clinicaltrials.gov (NCT 01589367). Written informed consent was obtained from all participants.

### Eligibility criteria and sample size calculation

Eligible patients are postmenopausal women with histologically confirmed ER-positive, stage II or III, primary breast cancer with palpable and clinically measureable tumors. The target population is 208 women, 104 in each arm. Sample size was calculated based on expected clinical response rates (cRR) of 55% in the letrozole plus placebo arm and 70% in the letrozole plus metformin arm, with α = 0.10 and 80% power and including an estimated 10% drop out rate. ER positivity is defined as ≥10% nuclear staining by immunohistochemistry or Allred score ≥3. Criteria for determining menopause include bilateral oophorectomy, age ≥60 years, or age <60 years and amenorrhea for ≥12 months and FSH >30 mIU/ml. Patients with diabetes (HbA1c ≥6.5% or fasting plasma glucose (FPG) ≥126 mg/dL (≥7 mM)); clinical T4, N3, or M1 disease; bilateral cancer, or inflammatory breast cancer will be excluded, as will patients with a history of lactic acidosis or at high risk of having metformin-induced lactic acidosis, such as those with high alcohol consumption or NYHA class III/lV congestive heart failure.

### Treatment schedule and evaluation

Patients will be randomly assigned (1:1) to 24 weeks of neoadjuvant treatment with metformin plus letrozole or placebo plus letrozole (Figure 1). Medications will be distributed at each monthly visit, with compliance assessed by counting the remaining tablets.

**Figure 1 F1:**
[figure not shown]
**Scheme of the METEOR trial.** Patients meeting the inclusion criteria will be 1:1 randomized to 24 weeks of letrozole plus metformin or letrozole plus placebo. Core needle biopsies will be recommended after 4 weeks of treatment. Surgery will be performed within 2 weeks after the end of the 24 week treatment period.

Tumor size will be measured clinically with calipers before treatment and sequentially every month. Each patient will undergo a careful physical examination at each monthly visit, and patients with progressive disease (PD) will be discontinued from the study and scheduled for immediate surgery. Patients with stable disease (SD) will be continued on treatment. Ultrasound-guided core needle biopsy samples will be obtained at the first visit and after four weeks of medication, with Ki67 levels in these samples centrally assessed. It is also recommended that 4-week blood samples be obtained to measure serum biomarker concentrations. Surgery will be scheduled within 2 weeks after completing the 24 weeks of medication. Tissue from surgical specimens will be collected for further planned assessments of biomarkers by paired analysis with the pretreatment and week 4 core needle biopsy specimens. HbA1c, FPG, insulin, c-peptide, and IGF-1 concentrations will be measured at baseline and after 12 and 24 weeks of treatment. Mammography, ultrasonography, and bilateral breast MRI will be performed before starting medication and after completion of treatment just before surgery.

### Analysis of the results

The primary endpoint is cRR. Tumor response will be assessed by RECIST criteria v1.1. Tumor size will be measured by individual clinicians at monthly visits. The secondary endpoint is pathologic complete response (pCR), defined as the absence of invasive cancer at the primary site and in the axilla. Before treatment, each patients will be categorized by surgeons into one of three groups: 1) marginal for breast conservation, 2) candidate for mastectomy only, and 3) inoperable by standard mastectomy [18]. Baseline assessment and actually performed surgery will be compared. The breast conservation rate in each arm will be evaluated, and the toxicity profile of each arm will be assessed every 4 weeks using NCI-CTCAE version 4.0 (http://ctep.cancer.gov/reporting/ctc.html). All parameters will be collected and managed using an e-clinical trial platform (MEBICA™).

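### The three baseline surgical groups leave no place for patients already suitable for breast conservation, so the comparison of baseline assessment with surgery performed cannot isolate surgery changed by treatment

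*Protocol article*

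**What the plan says.** The article's section on analysis of the results states that "each patients will be categorized by surgeons into one of three groups", and lists them as "1) marginal for breast conservation, 2) candidate for mastectomy only, and 3) inoperable by standard mastectomy". This is done before treatment. The same section gives the use of the grouping: "Baseline assessment and actually performed surgery will be compared". It then adds a separate item: "The breast conservation rate in each arm will be evaluated". The abstract also names the conservation rate among the secondary endpoints: "Secondary endpoints include pathologic complete response rate, breast conserving rate".

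The eligibility section admits postmenopausal women with "histologically confirmed ER-positive, stage II or III, primary breast cancer with palpable and clinically measureable tumors". It states that patients with "clinical T4, N3, or M1 disease; bilateral cancer, or inflammatory breast cancer will be excluded". It gives no minimum tumour size and no condition that conservation be unsuitable or only marginal at entry.

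**The concern.** The grouping covers every patient, and its most favourable level is marginal. Eligibility, as written, lets in patients whose position is better than that. The scale therefore stops short of the enrolled population at its most operable end.

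The purpose of recording a baseline surgical assessment is to show whether neoadjuvant treatment changed the operation. That needs a record of which patients had conservation open to them beforehand. If those patients are filed with the marginal ones, conservation that needed no treatment looks like conservation that treatment made possible. If they are left unclassified, they drop out of the comparison without a rule. Either way the defect arises when the data are collected, so an analysis plan written later cannot repair it.

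**Working it through.** **1. Plan figures.** The article gives no expected conservation or conversion rate and no share of patients suitable for conservation at entry, so there is no figure to reproduce on this point. The 104 patients per arm were derived from clinical response rates of 55% and 70%. The surgical groups do not enter that calculation.

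**2. Population against categories.**

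| Position at baseline | Excluded by the eligibility text? | Group provided? |
|---|---|---|
| Clearly suitable for conservation | No | None |
| Marginal for conservation | No | Group 1 |
| Mastectomy only | No | Group 2 |
| Inoperable by standard mastectomy | Partly (T4, N3 and inflammatory disease are out) | Group 3 |

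The first row is the gap.

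**3. What the comparison can show.** Cross-classify baseline group against surgery performed. A suitable patient who has conservation falls in the cell for group 1 with conservation, or in no cell. A truly marginal patient whose tumour shrank falls in that same cell. Nothing recorded distinguishes the two. If misplaced patients enter only group 1, the mastectomy-only row keeps its meaning.

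**4. Illustrative size.** All inputs are assumptions:
- *s* = share already suitable at entry, taken as 20%, 30% and 50%;
- 95% of those patients have conservation;
- 40% of the remaining patients have conservation;
- groups 1 to 3 are pooled and every conservation is read as a conversion.

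Apparent conversion = 0.95*s* + 0.40(1 − *s*). Share of conservations that are not changes = 0.95*s* ÷ apparent conversion.

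| *s* | Apparent conversion | Value among patients not suitable | Share that are not changes |
|---|---|---|---|
| 20% | 0.19 + 0.32 = 51% | 40% | 0.19/0.51 = 37% |
| 30% | 0.285 + 0.28 = 56.5% | 40% | 0.285/0.565 = 50% |
| 50% | 0.475 + 0.20 = 67.5% | 40% | 0.475/0.675 = 70% |

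**5. Effect on the contrast between arms.** Let the rate among patients not suitable be 40% in one arm and 55% in the other, with 95% among suitable patients in both. The all-patient difference is 15(1 − *s*), which is 12, 10.5 or 7.5 points. This formula contains nothing about how patients were grouped. The all-patient rate, and so the difference, is the same with three categories or four. The shrinkage comes from who is enrolled and is not a consequence of the grouping.

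**6. Direction.** The grouping precedes treatment, allocation is 1:1 ("Patients will be randomly assigned (1:1) to receive letrozole 2.5 mg/day plus either metformin or placebo") and study personnel are masked. Misplacement should therefore be equally frequent in both arms. It raises apparent conversion in each and should favour neither.

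**The case against.** A reader might infer that the secondary endpoint itself counts non-conversions as conversions. The article does not support that. The named endpoint is the conservation rate per arm, which counts conservation whatever the baseline group. No conversion is defined, and the baseline comparison has no counting rule. The percentages in the table need two steps that the text does not state: suitable patients filed as marginal, and all groups pooled.

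A reader might also blame the grouping for the fall from 15 to 7.5 points. Step 5 shows that this is wrong, and the all-patient difference remains a valid randomised comparison.

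A third tempting reading is that group 3 is empty and therefore harmful. The exclusions probably make it sparse, but that is a clinical inference: inoperability is not defined, and not all stage III disease is excluded. A sparse group biases nothing.

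Finally, this is a condensed article. The full eligibility criteria may be narrower, and the groups are cited to an outside source not available here, so how marginal is to be applied is unknown. This objection limits confidence but does not remove the point. The article presents the list as complete and applies it to each patient, and that list does not fit the population the article describes. If the full protocol restricts entry to patients not suitable for conservation, the gap closes.

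**Conclusion.** The point holds in a limited form. The stated groups do not cover the eligible population as described, and the comparison of baseline assessment with surgery performed cannot tell changed surgery from surgery already possible.

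Its size cannot be determined from the documents. Under the assumed rates and with pooling, apparent conversion would be 51% to 67.5% in place of 40%, for 20% to 50% already suitable. These figures show only what the chosen inputs produce.

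No bias between arms is expected. The primary endpoint, the sample size and the all-patient conservation rate per arm stand as they are. The change is worth making because it is cheap and because the information, if not recorded at baseline, is lost.

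**What to change.** - Add a fourth baseline category, suitable for breast conservation, and record it before randomisation.
- Keep the conservation rate in all randomised patients, by arm, as the secondary endpoint.
- Report baseline assessment against surgery performed separately for each baseline group. Count a change in surgery only among patients not suitable at baseline.
- Show the marginal group apart from the mastectomy-only group. Some marginal patients might have had conservation without treatment, so pooling the two would bring back part of the same ambiguity.

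The cost is one extra option on the case report form and one definition in the analysis plan. The change-in-surgery comparison has a smaller denominator: of 208 patients, about 166 (208 × 0.80) to 104 (208 × 0.50) if 20% to 50% were already suitable. The sample size does not change. For patients already enrolled, the category could be assigned only from records made before treatment, and such cases should be flagged.

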### Translational research project

In addition to assaying Ki-67, phosphorylated S6 kinase 1 (p-S6K1) will be analyzed by immunohistochemistry (IHC) in a central laboratory. Fresh frozen tissue of week 4 biopsies and final surgical specimens will be collected from several major hospitals participating in this study. These samples will be used for DNA microarray analysis or whole transcriptome sequencing using next generation sequencing (NGS) technology. Phosphorylation of AMPK(T172), expression of IR(insulin receptor) and OCT1(Organic cation transporter) will be measured. Assessment of apoptosis will be done by Miller-Payne Grading system along with various commercialized kits.

We previously reported that breast density reduction after short term adjuvant endocrine therapy was predictive of recurrence-free survival [19]. We intend to analyze the association between breast density reduction and response to endocrine therapy in this prospective trial. Pre- and post-medication mammography results and breast MRI images of all patients will be centrally reviewed. Breast density will be measured centrally using computer-assisted software, Cumulus (University of Toronto, Toronto Ontario, Canada), by a single observer. The density of both breasts will be assessed by breast MRI [20], with the cranio-caudal view of the contralateral breast used as a reference to evaluate the percent change in mammographic density.

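### Breast density is evaluated as percent change, which is unstable where baseline density is low; a baseline-adjusted analysis of the same readings is the better measure

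*Protocol article*

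**What the plan says.** The Abstract (Methods/Design) of the protocol article states: "Secondary endpoints include pathologic complete response rate, breast conserving rate, change in Ki67 expression, breast density change, and toxicity profile". Density change is therefore a secondary endpoint of a randomised, placebo-controlled comparison.

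The section Translational research project gives the method. "Breast density will be measured centrally using computer-assisted software, Cumulus", by one observer, "with the cranio-caudal view of the contralateral breast used as a reference to evaluate the percent change in mammographic density". A second modality is also named: "The density of both breasts will be assessed by breast MRI", with no scale given. The only density analysis described there is this: "We intend to analyze the association between breast density reduction and response to endocrine therapy in this prospective trial".

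The section Treatment schedule and evaluation fixes the timing: "Mammography, ultrasonography, and bilateral breast MRI will be performed before starting medication and after completion of treatment just before surgery". Each woman thus has one reading before treatment and one after.

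The article does not say whether percent change is relative or in percentage points. It also does not say whether density is a proportion of the breast or an absolute dense area. Eligibility requires postmenopausal status and sets no lower limit on density.

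**The concern.** Percent change is the only mammographic scale the article names, and it has two possible weaknesses.

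The first is division by baseline. When the baseline is small, an ordinary reading error becomes a large percentage. A few women with near-fatty breasts can then carry most of the variance, which costs precision in the arm comparison and blurs the relation between density reduction and response.

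The second applies only if density is the dense share of the breast. Its denominator then includes fat, so the share moves when fat changes even if dense tissue does not. Should fat loss differ between the arms, part of the density contrast would reflect fat.

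At stake is the usefulness of one secondary endpoint and one translational analysis.

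**Working it through.** **The plan's own figures.** The article gives no effect size, power or sample size for density. Its 104 per arm is derived from clinical response rates, and this point does not bear on it.

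**1. Division by baseline**

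Inputs: two readings per woman (Treatment schedule and evaluation). The reading error SD, e, is assumed to be 1 to 2 percentage points per film, independent between films and equal at all baselines. Baseline densities of 5%, 10%, 20% and 30% are illustrative. The documents give neither the error nor the density distribution.

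For small true change, the error SD of relative change is approximately √2 × e / baseline.

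| Baseline density | e = 1 point | e = 2 points |
|---|---|---|
| 5% | 1.414/5 = 28% | 2.828/5 = 57% |
| 10% | 14% | 28% |
| 20% | 7% | 14% |
| 30% | 5% | 9% |

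For any constant e, a woman at 5% has (30/5)² = 36 times the error variance of a woman at 30%. If the error is smaller at low density, say 1 point at 5% and 2 points at 30%, the SDs are 28% and 9%, still about threefold apart.

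If percent change means percentage points, there is no division. The error SD is then √2 × e, or 1.4 to 2.8 points, at every baseline.

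**2. Dependence on fat, if density is dense area over total area**

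Let percent density = D/(D + F), with dense area D and non-dense area F. The falls in F are assumed; the documents give none. Start with D = 10 and F = 90, a baseline of 10%.

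| Fall in F | D unchanged | D truly down 10% |
|---|---|---|
| 0% | 10/100: no change | 9/99 = 9.09%: −9.1% |
| 3% | 10/97.3 = 10.28%: +2.8% | 9/96.3 = 9.35%: −6.5% |
| 5% | 10/95.5 = 10.47%: +4.7% | 9/94.5 = 9.52%: −4.8% |
| 10% | 10/91 = 10.99%: +9.9% | 9/90 = 10.00%: 0.0% |

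At a baseline of 25%, the same falls of 3%, 5% and 10% in F with D unchanged give +2.3%, +3.9% and +8.1%. When D and F shrink by the same proportion, the ratio does not move at any baseline. Absolute dense area has no F term.

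**3. Which weakness applies under which reading**

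| Meaning of percent change | Divides by baseline | Contains fat |
|---|---|---|
| Relative change in percent density | yes | yes |
| Relative change in dense area | yes | no |
| Percentage-point change in percent density | no | yes |

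Each reading has at least one of the two. Baseline-adjusted dense area has neither.

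**The case against.** The strongest reply is that much of this depends on what the article leaves open. It never defines density as a ratio, and a full protocol or analysis plan may fix the scale and the covariates. This stands in part: the missing definition is no finding. The point is confined to the scale the article does state, and every reading of that scale has one of the two weaknesses.

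A reader might infer that metformin causes weight loss and so biases the density comparison. The documents do not support this. No section mentions an effect on weight or breast fat. The Background says "the anti-cancer effects of metformin are mediated through a systemic improvement in metabolic profile", but explains it through circulating insulin and IGF. Weight could change in either arm. Fat loss raises the ratio, so it could mask a fall in density or mimic a rise; it could not mimic the reduction that interests the investigators.

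Random reading error does not favour an arm either. Study personnel are masked and a single central observer reads the films. The consequence is lost precision and a weaker association, not directional bias. The error SD and the presence of many low baselines are both assumed.

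Two further replies carry some weight. The only density analysis described is the association with response; the arm comparison is implied by the list of secondary endpoints. MRI is a second density measure, but with its scale unstated it cannot be counted on as a safeguard.

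**Conclusion.** The point holds as a minor improvement to a secondary endpoint. If percent change is relative, reading error alone gives an SD of about 28–57% at a baseline of 5% and about 5–9% at 30%. This rests on an assumed error of 1 to 2 points and on low baselines occurring, which eligibility permits but the article does not quantify. The result is inefficiency and undue influence of near-fatty breasts.

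The dependence on fat is conditional twice over: on density being a dense-to-total ratio, and on fat loss differing between arms. The documents establish neither. It justifies reporting dense area alongside, but not a claim that the comparison is biased. The primary endpoint and the sample size are untouched.

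**What to change.** Before unblinding, state the density analysis as follows:

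- Compare arms on post-treatment contralateral mammographic density, with baseline density as a covariate, instead of on percent change.
- Report the same baseline-adjusted analysis for absolute dense area from the same readings, alongside percent density.
- In the analysis relating density to response, use post-treatment density adjusted for baseline instead of percent change.
- Keep percent change as a descriptive table.
- Do not adjust the arm comparison for weight change. Weight change arises after randomisation and may itself be affected by treatment, and the article lists no weight or BMI measurement.

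The cost is a change of analysis wording. Images, software and observer stay the same, on the assumption that the readings provide dense area. The downside is slightly less direct comparability with earlier reports that used percent change, which the descriptive table largely meets.
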